## Abstract

**Background:** One in every four patients with a first episode of non-gallstone-related acute pancreatitis (AP) develops recurrent disease. Recurrent episodes of AP or acute flares of chronic pancreatitis (CP) are associated with decreased quality of life and progression of the disease. Besides removing the etiology of pancreatitis (which sometimes is not possible), there are no effective measures to prevent recurrence. Meta-analyses of randomized controlled trials, as well as epidemiological and cohort studies, suggest that statins may be protective against the development of index AP.

**Methods:** The SIMBA study is a triple-blind randomized placebo-controlled, parallel-group multicenter trial. Patients with recurrent AP or with acute flares of CP (at least two episodes in the last 12 months) will be randomized to receive simvastatin 40 mg daily or placebo. During a 3-year study period, 144 patients (72 per arm of treatment) from 26 centers will be enrolled. The patients will receive the study treatment for 1 year. The primary aim is to compare the recurrence of AP or acute flares in CP. Secondary endpoints include the incidence of new-onset diabetes mellitus, new-onset exocrine pancreatic insufficiency (EPI), new-onset imaging signs of CP, frequency of all-cause hospital admissions, severity of AP, adherence to treatment, and frequency of adverse events.

**Discussion:** The SIMBA trial will ascertain whether simvastatin, a safe, widely used and inexpensive drug, can change the natural course of recurrent pancreatitis.

**Trial Registration**: ClinicalTrials.gov Identifier: NCT04021498

## Introduction

Acute pancreatitis (AP) is the third most common cause of hospital admission due to gastrointestinal disease (1). Gallstones and excessive alcohol intake account for most cases of AP. Recurrent AP (RAP) refers to the development of at least two separate documented episodes of AP with a period of resolution in between (2). Approximately 20% of the patients will relapse after a first episode of AP (2, 3). The approximate incidence of recurrent AP is likely 8–10 per 100,000 per year, and its prevalence is 110–140 per 100,000 populations (2). The relatively low frequency of relapse in biliary AP (close to 10%) (3) is due to the high effectiveness of cholecystectomy (4), but a first episode of AP due to alcoholic or other etiologies is associated with relapse in one in every four patients (2, 3). Currently, besides removing etiological factors (which is frequently not possible), there are no specific medical treatment that changes the natural history of RAP. RAP is an intermediate stage in the pathogenesis of chronic pancreatitis (CP) as a subset of RAP patients' transition to CP (one in every three patients) over their natural history (2, 5). Forty-five percent of patients with CP experience intermittent flares of pain according to a prospective cohort study (6). Intermittent pain in CP is associated with missed days of work, frequent need for hospitalization, and a decreased quality of life (6).

Statins are drugs that inhibit 3-hydroxy-3-methyl-glutaryl-coenzyme A reductase, the rate-controlling enzyme in the cholesterol synthetic pathway, resulting in decreased serum levels of total and low-density lipoprotein cholesterol. Besides this, statins may have anti-inflammatory properties (7). Some studies suggest that statins have an important effect on the incidence and severity of AP (8). A meta-analysis of randomized controlled trials showed that statin use was associated with a decreased risk of AP (9). A retrospective cohort study based on data from an integrated health care system suggested that simvastatin is independently associated with a lower probability of having an episode of AP (adjusted risk ratio 0.626, 95% confidence interval 0.588–0.668) (10). Furthermore, some studies have shown decreased severity of AP among consumers of statins (11, 12). We hypothesized that simvastatin, a widely used patent-free statin, reduces the number of new episodes of AP or inflammatory relapses in CP in patients with recurrent pancreatitis. The main aim of SIMBA (**SIM**vastatin in the prevention of recurrent pancreatitis, a triple **B**lind r**A**ndomized controlled multicenter trial) is to compare the recurrence rate of AP in patients with recurrent pancreatitis consuming simvastatin vs. placebo.

## Patients and Methods

### Design

SIMBA is a triple-blind randomized placebo-controlled, parallel-group, superiority multicenter trial. This final protocol (version 4) was finished on June 6th, 2018. This study protocol follows the SPIRIT guidelines (13).

### Participating Centers

The members of the Spanish Association of Gastroenterology (AEG) and the Spanish Association of Pancreatology (AESPANC) were invited to participate in the study between January 2016 and October 2017. Currently (April 2020), 32 Spanish centers and 1 Indian center have agreed to join or are currently recruiting patients.

### Primary Endpoint

The primary endpoint is recurrence of pancreatitis during the 1-year follow-up period (meaning a new attack of AP or acute flares in CP). The definition of recurrent pancreatitis, both in AP and CP, requires at least two of the following three features: (i) typical acute pancreatic abdominal pain (acute onset of a persistent, severe, epigastric pain often radiating to the back); (ii) serum lipase activity (or amylase activity) at least three times greater than the upper limit of normal; and (iii) characteristic findings of pancreatic inflammation on contrast-enhanced computed tomography (CECT) and less commonly magnetic resonance imaging (MRI) or transabdominal ultrasonography (14). Although this definition was originally intended for AP (14), in SIMBA, it is also used to define acute flares of pain and inflammation in CP. Patients with CP and pain without increased serum pancreatic enzymes and/or signs of new-onset inflammation on imaging are not considered as having an inflammatory flare.

### Secondary Endpoints

New-onset diabetes at the end of follow-up, according to the American Diabetes Association criteria (15). Blood levels of glycosylated hemoglobin at the end of follow-up will also be compared to baseline.New-onset exocrine pancreatic insufficiency (EPI) defined by fecal elastase-1 <100 mcg/g (16). Fecal elastase-1 levels at the end of follow-up will also be compared to baseline.Imaging signs of CP at the end of follow-up, defined as calcifications and/or dilated pancreatic duct (≥4 mm) (17), mainly on a CT scan, but endoscopic ultrasound and/or MRI are allowed, particularly in younger patients to avoid excessive exposure to ionizing radiation.Frequency of all-cause hospital admissions.Severity of AP according to the revision of the Atlanta Classification (moderate-to-severe vs. mild) (14).Adherence to treatment (percentage of the planned treatment consumed by the patient).Frequency of adverse events.

### Study Population

Patients with recurrent pancreatitis managed in the outpatient setting of the recruiting centers are potential candidate subjects for the study. The acute episode of pancreatitis, or acute flares of pain in CP, may have been treated in other centers; however, patients are eligible for recruitment only when all the required information is available. Patients that meet the inclusion and have no exclusion criteria receive detailed information about the study and are asked for written consent to participate.

#### Inclusion Criteria

Adult (≥18) patients.At least two episodes of AP or acute flares of CP, defined according to the Revised Atlanta Classification (14).Written informed consent to participate in the study.

#### Exclusion Criteria

Less than two episodes of AP or acute flares of CP in the last 12 months.Statin consumption in the previous year.Contraindications to the use of statins (myopathy, allergy, severe liver disease, and drugs that inhibit CYPP3A4).Cholelithiasis or choledocholithiasis diagnosed in the last episode of AP (every patient must have at least one abdominal ultrasonography and a magnetic resonance cholangiopancreatography and/or endoscopic ultrasonography ruling out cholelithiasis to enter the study).Endoscopic sphincterotomy and/or cholecystectomy and/or pancreatic surgery between last episode of pancreatitis and recruitment or patients who are expected to undergo any of these interventions within the next year.Serum triglycerides >500 mg/dl without previous specific treatment before the last episode of pancreatitis or patients expected to have a change in their specific hypertriglyceridemia treatment in <1 year.Primary hyperparathyroidism that has been operated between last episode of pancreatitis and recruitment or will be operated in <1 year.Iatrogenic AP (pancreatitis due to endoscopic retrograde cholangio-pancreatography, surgery, or after other invasive treatment). Iatrogenic pancreatitis will not count as an episode of recurrent pancreatitis, but patients may be included in the study if they meet the other inclusion and exclusion criteria, specially exclusion criteria number 5.Abstinence syndrome due to alcohol or drugs and/or delirium tremens in the last 6 months before recruitment.Previous (last year) failure to attend follow-up medical visits or lack of adherence to treatment, or social problems that may be associated to lack of adherence to the study treatment or to inadequate follow-up.Pregnancy and breast-feeding.

### Flowchart According to Consort

The flowchart for the SIMBA trial will be based on the CONSORT recommendations (18, 19) and SPIRIT guidelines (13) (Figure 1).

**Figure 1 F1:**
[figure not shown]
Flowchart for SIMBA trial according to CONSORT 2010 and SPIRIT 2013 recommendations. **(A)** ≥18 years old, at least 2 episodes of AP or acute flares of chronic pancreatitis, written informed consent. **(B)** <2 episodes of pancreatitis or acute flares of chronic pancreatitis in the last 12 months; stain consumption in the previous year; contraindications to the use of statins; cholelithiasis or choledocholithiasis diagnosed in the last episode of pancreatitis; endoscopic sphincterotomy and/or cholecystectomy and/or pancreatic surgery between last episode of AP and recruitment or patients who are expected to undergo one of this techniques in less than a year; serum triglycerides >500 mg/dL without previous specific treatment before the last episode of pancreatitis, or in patients expected to have a change in their specific hypertriglyceridemia treatment in <1 year; primary hyperparathyroidism that has been operated between last episode of pancreatitis and recruitment or will be operated in <1 year; iatrogenic pancreatitis; abstinence syndrome due to alcohol or drugs and/or delirium tremens in the last 6 months before recruitment; previous (last year) failure to attend follow-up medical visits, social problems that may be associated to failure to take the medication or to perform an adequate follow-up; pregnancy or breastfeeding. **(C)** Intention-to-treat (primary analysis) and per-protocol analysis. T_x_, treatment.

### Treatment Protocol

Patients receive simvastatin 40 mg or placebo, one capsule daily for 1 year. In case of recurrence of AP or acute flares of CP, the patients are advised to continue the treatment as planned. Adherence to treatment is monitored in each outpatient visit (comparison of the number of capsules remaining in the container with the number of capsules that should remain).

According to patient exclusion criteria, endoscopic retrograde cholangio-pancreatography, parathyroid, biliary, and/or pancreatic surgery are discouraged during the treatment period. In case of undergoing any of these procedures, the patient will be included in the intention-to-treat analysis, but the Trial Steering Committee will decide whether that patient should be included in the per-protocol analysis or not (the decision will be taken before blinded statistical analysis).

### Data Management

Clinical data are collected by the study recruiters (gastroenterologists from the participating centers) by means of a standardized electronic case report form (CRF) based on REDCap (22). Access to REDCap is provided by the Spanish Association of Gastroenterology, AEG (AEG REDCap node). The CRF does not contain the name, initials, or any personal identification number from the patients. Each patient is identified in the CRF by a double registration number: center and patient. Only the recruiting gastroenterologists, in direct charge of managing the patient, have access to the patient identity. The CRF has been designed to help promote data quality (including range checks for dates and quantitative data values).

### Independent Trial Steering Committee

The role of the Trial Steering Committee (TSC) is (1) to monitor and supervise the progress of the trial toward its objectives, (2) to review at regular intervals relevant information from other sources (i.e., other related trials), (3) to consider the recommendations of the DMC, and (4) to advise the Principal Investigator (PI) on the presentation of all aspects of the trial (24). The members of the TSC are [name], [name], and [name].

### Safety

Simvastatin is a widely consumed and safe drug. The collaborating investigators must report immediately any possible adverse reaction. The DMC will be in charge for safety monitoring. In case of a potentially severe adverse reaction, the DMC will consider unblinding that particular patient, if medically advised. The DMC will periodically review the unblinded safety variables. The DMC will contact the Spanish Drug Agency (Agencia Española de Medicamentos y Productos Sanitarios, AEMPS) and the Central Drugs Standard Control Organization (CDSCO) from India, as well as the regional health authorities in case of safety issues.

### Statistical Aspects

For all statistical analysis, the threshold for defining statistical significance will be 0.05.

#### Sample Size Calculation

Based on a pilot retrospective internal non-published analysis of patients from AUGH meeting the study inclusion and exclusion criteria, a recurrence rate of 50% in 1 year in patients with placebo is expected. We powered the study to detect a 50% decrease in recurrence during the study period. According to the arcsine method, with an alpha level of 0.05, a statistical power of 80%, an expected 1-year recurrence in the placebo arm of 50 and 25% in the simvastatin arm, and a 20% loss of follow-up, 144 patients are needed (72 per treatment arm).

#### Descriptive Statistics

Continuous data will be evaluated for normality by the Shapiro–Wilk test and will be summarized using mean and standard deviation or median and interquartile range depending on the variable distribution. Qualitative data will be displayed as *n* (%). Baseline criteria are age, gender, diagnoses of CP, number of episodes of AP or acute flares of CP (lifetime episodes as well as episodes in the 12 months prior to recruitment), etiology, active consumption of alcohol (any alcohol and ≥5 drinks per day) (25), active smoking (25), body mass index, diabetes mellitus (15), and pancreatic exocrine insufficiency (fecal elastase-1 <100 mcg/g).

#### Analysis

For blinded statistical analysis, the Clinical Pharmacology Department of AUGH will provide for every patient included in the study a label: “A” or “B.” After statistical analysis, labels A and B will be unblinded as placebo or simvastatin. Both intention-to-treat (primary analysis) and per-protocol analysis will be performed.

Recurrence of AP or acute flares of CP during the follow-up period will be analyzed as a dichotomous variable (primary analysis and variable used for sample calculation): recurrence during follow-up yes/no, by means of the Chi-square test as well as the Kaplan–Meier time-to-event test, and as a quantitative variable (secondary endpoint): number of episodes of AP or acute flares of CP during follow-up and decrease in the number of episodes in respect to the previous year by means of the *t*-test and pairwise *t*-test, respectively. In case of a non-parametric distribution, the Mann–Whitney *U* test or Wilcoxon test will be performed.

Similarly, for other secondary endpoints, we will use Chi-square test, *t*-test/Mann–Whitney *U* test, or pairwise *t*-test/Wilcoxon test according to the characteristics of the variables. Incidence rate ratio will be used to analyze the reduction in total number of AP events or acute flares of CP per arm of treatment.

Odds ratio (95% confidence interval) will be used for quantifying effect size when applicable. Pre-specified subgroup analysis: patients with AP and patients with CP.

In case of significant difference in the baseline distribution of any variable, multivariate analysis (binary logistic regression) will be used to correct it.

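### The decrease in episodes from the previous year is tested with a paired test that contains no simvastatin–placebo contrast, in patients selected for a high count in that year

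*Protocol article*

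**What the plan says.** The Analysis section of the protocol article treats the number of episodes as a quantitative secondary endpoint in two forms: the count during follow-up, and the "decrease in the number of episodes in respect to the previous year by means of the" t-test and pairwise t-test. The two tests are assigned to the two measures in order. The two-sample t-test therefore belongs to the follow-up count and the pairwise t-test to the decrease. The fallback keeps the same order: the "Mann–Whitney *U* test or Wilcoxon test will be performed". No between-arm test of the decrease is named.

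The next paragraph adds a rate comparison: "Incidence rate ratio will be used to analyze the reduction in total number of AP events or acute flares of CP per arm of treatment".

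Three other places bear on the point:

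- Exclusion Criteria rule out patients with "Less than two episodes of AP or acute flares of CP in the last 12 months".
- Sample Size Calculation states that "a recurrence rate of 50% in 1 year in patients with placebo is expected".
- Descriptive Statistics lists the prior counts among the baseline data: "lifetime episodes as well as episodes in the 12 months prior to recruitment".

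For two laboratory measures, Secondary Endpoints says "Blood levels of glycosylated hemoglobin at the end of follow-up will also be compared to baseline" and "Fecal elastase-1 levels at the end of follow-up will also be compared to baseline". The Analysis section allows two-sample or paired tests for the other secondary endpoints, depending on the variable.

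**The concern.** A paired test on a patient's two yearly counts asks whether this year differs from last year. It has no treatment term. Run in each arm or on all patients pooled, it cannot say whether simvastatin differs from placebo.

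Here the answer to the question it does ask is largely fixed by the design. Everyone is admitted because the previous year was bad, with two episodes or more. The plan itself then expects half the placebo arm to have no episode in the following year. A large fall follows from selection and chance variation (regression to the mean), without any drug effect.

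At stake is a pre-specified p-value that would be very small and could be reported as a significant reduction in episodes on simvastatin, even if the drug does nothing.

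**Working it through.** **1. The plan's own figure.** Inputs from Sample Size Calculation: 50% versus 25% recurrence, alpha 0.05 (two-sided assumed), power 80%, 20% loss, arcsine method.

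- h = 2·asin(√0.50) − 2·asin(√0.25) = 1.5708 − 1.0472 = 0.5236
- n per arm = 2·((1.960 + 0.842)/h)² = 57.26
- 57.26/0.8 = 71.6, so 72 per arm and 144 in total. The stated size is reproduced.
- Analysed per arm after 20% loss: 72 × 0.8 = 57.6, taken as 58.

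**2. Break-even without a distribution.** Every patient has at least 2 prior-year episodes, and 50% are expected to recur on placebo. The placebo mean stays level only if 0.5 × (episodes per recurrer) is at least 2, that is, at least 2/0.5 = 4 episodes per recurrer. Any prior-year mean above 2 raises this threshold.

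**3. Expected fall with no drug effect.** The documents give no count distribution, so one is assumed: each patient has a constant rate over both years, rates are gamma with shape k and mean μ, and counts are Poisson. Only patients with a prior-year count x ≥ 2 are kept. Given x, the rate is gamma with shape k + x and rate parameter b = k/μ + 1. The expected follow-up count is then (k + x)/b, and the probability of no episode is (b/(b + 1))^(k + x). The mean μ is solved so that 50% recur.

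Worked case, k = 1: μ = 0.309, b = 1/0.309 + 1 = 4.236, mean prior count 2.309, follow-up mean (1 + 2.309)/4.236 = 0.781.

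| Shape k | Prior-year mean | Follow-up mean | Fall |
|---|---|---|---|
| 0.5 | 2.32 | 0.80 | 65% |
| 1 | 2.31 | 0.78 | 66% |
| 2 | 2.30 | 0.76 | 67% |
| 5 | 2.28 | 0.73 | 68% |

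These follow-up means imply about 1.5 to 1.6 episodes per recurrer (0.73/0.5 to 0.80/0.5), far below the break-even of 4.

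**4. How often the paired test is significant with no drug effect.** With 58 patients at 50% recurrence, the paired t-test (1,000 simulated arms) and the Wilcoxon test (300) showed a significant decrease in 100% of arms for every shape in the table. At 60% recurrence the figure is again 100%; at 70% it is 99.9–100%.

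**5. Check without the gamma-Poisson model.** Set every patient at exactly 2 prior episodes, let 50% recur, and give each recurrer 1 + Poisson(a) episodes (2,000 simulations, n = 58).

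| Mean episodes per recurrer | Probability of a significant decrease |
|---|---|
| 1.5 | 100% |
| 2 | 99.95% |
| 2.5 | 94% |
| 3 | 53% |
| 4 | 3% |

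Hand check at 3 per recurrer: mean decrease 2 − 1.5 = 0.5; variance 0.5 × (2 + 9) − 1.5² = 3.25; standard error √(3.25/58) = 0.237; ratio about 2.1, in line with 53%.

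**6. Between-arm tests on the same null data.** With two untreated arms of 58, 50% recurrence and shapes 0.5, 1 and 2, the paired t-test was significant in both arms in 100% of 2,000 trials. A two-sample test of the change rejected in 4.7–5.0%, and a two-sample test of the follow-up count in 4.2–5.3%. The fault lies in the choice of test, not in the data.

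**The case against.** The strongest reply is that little depends on this analysis. The primary analysis is recurrence yes or no by Chi-square and Kaplan–Meier, and the sample size rests on it. The Analysis section also plans a two-sample test of follow-up counts and an incidence rate ratio by arm. Regression to the mean acts on both randomised arms alike, so all of these remain valid. A reader might infer that the trial's main conclusion is compromised, or that no between-arm comparison of episode counts is planned; the documents support neither. This part of the objection stands and sets the severity.

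Three further limits also stand.

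- The text does not say that the paired test is run within each arm. That is an inference; a pooled test is also possible. Neither version contains a treatment contrast, so the point survives.
- A reader might expect the usual trap of one arm significant and the other not. For episodes, under the model used here, both arms are significant in practically every trial. If both arms are reported, placebo would show a similar fall beside simvastatin.
- A reader might extend the selection argument to HbA1c and faecal elastase. Patients are not selected on either, so it does not carry over. New-onset diabetes and new-onset exocrine insufficiency are separate secondary endpoints for which the Chi-square test is available, and the plan also allows two-sample tests for other secondary variables.

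The reply does not rescue the paired test. The other analyses answer the treatment question properly, but the uninformative p-value would still be pre-specified and available for reporting.

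**Conclusion.** The point holds as a moderate error confined to one secondary analysis. The test assigned to the decrease from the previous year cannot show a treatment effect, and under the plan's own 50% placebo recurrence it is nearly certain to be significant when there is none.

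The size (a fall from about 2.3 to 0.73–0.80 episodes, with 100% of untreated arms of 58 significant) rests on assumed gamma-Poisson rates that stay constant over two years. It is not a mathematical necessity: with everyone at two prior episodes, the probability is 94% at 2.5 episodes per recurrer and 53% at 3, and the effect vanishes near 4.

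For HbA1c and faecal elastase there is a lesser, separate point: a change from baseline alone cannot separate a drug effect from the course of the disease.

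**What to change.** - Report the change in episodes from the previous year by arm as description, without a p-value.
- Test the treatment effect on episodes between arms with a count model of follow-up episodes (Poisson with robust standard errors, or negative binomial). Include treatment, the prior-year count as covariate and log follow-up time as offset. This can also be the stated method for the planned incidence rate ratio.
- Compare 12-month HbA1c and faecal elastase between arms by ANCOVA adjusted for the baseline value, with elastase on the log scale if skewed.

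The cost is a few sentences in the plan and a few lines of code. Prior-year counts are listed as baseline data under Descriptive Statistics, and both laboratory measures are taken at baseline and at the last visit under Recruitment and Follow-Up. No new data and no change in sample size are needed.
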